### Irradiation of the lymphatics

In both arms irradiation of the lymphatics will be performed when indicated, according to the S3 guidelines of the German Cancer Society [16].

Irradiation of the axillary lymph nodes is recommended in following cases:

• Presence of residual tumor in the axilla

• Clinically apparent tumor spread to the axilla or in case of positive sentinel node biopsy without or after incomplete axillary dissection

Irradiation of the supra-/infraclavicular lymph nodes is recommended in following cases:

• When more than 3 lymph node are positive

• In case of tumor spread to level III

### Follow up

The first radio-oncologic follow-up is planned 6 weeks after treatment completion. Further trial related follow-up visits are scheduled at 2 years and 5 years post treatment. In the time between 6 weeks and 2 years, as well as between 2 and 5 years post treatment, follow-up examinations are conducted by the attending gynecologists, according to the guidelines of the German Cancer Society.

Evaluation of the cosmetic result is conducted 6 weeks and 2 years post treatment. For complete evaluation of overall survival, disease free survival, as well as possible late side-effects, e.g. secondary cancer, a follow-up period of 15 years is necessary. Therefore, further trial related documentation will be performed at 10 and 15 years post treatment.

An overview of trial related follow-up is shown in Figure 2.

**Figure 2 F2:**
[figure not shown]
**Trial follow-up**.

### Evaluation

The cosmetic result is evaluated via photo-documentation. Before radiotherapy, 6 weeks and 2 years post treatment photographs of the patient's torso are taken in a standardized way: 2 frontal photographs from neck to midabdomen (one with arms raised and one with both arms alongside the body) and a profile photograph of the treated breast (arms raised). The pictures are evaluated by two independent investigators. Parameters to be evaluated are skin color, teleangiectasy, scars, shrinking and asymmetry. Evaluation is also carried using a quantitative digitizer scoring system, as described by Vrieling et al. [17]. Four positions are scanned on a frontal view patient photo: the mark at suprasternal notch, the mark at the midline 25 cm inferior to the suprasternal notch, the nipple position of the treated breast and the nipple position of the untreated test. These are used for the calculation of a breast retraction assessment (BRA) score. Furthermore, cosmetic evaluation is based on the standards set forth by the Harvard criteria [18]. An excellent score is given when the treated breast looks essentially the same as the contralateral, untreated breast. A good score is given for minimal but identifiable radiation effects on the treated breast, while a fair score is assigned for significant radiation effects. A poor score is used for severe sequelae of the treated breast.

Tumor manifestations within the residual breast, the regional lymphatics (axillary, parasternal, infra-/supraclavicular) or the radiation field borders are defined as locoregional relapse. Other types of tumor recurrence are considered distant metastases.

Secondary cancers must be confirmed by histological analysis. The results of the analysis should not be consistent to the original histology of the primary tumor. Date and way of diagnosis, as well as the applied dose at the site of origin of the second malignoma are documented.

Quality of life is assessed by means of the EORTC questionnaire QLQ-C30 and the breast cancer questionnaire QLQ-BR23 at 6 weeks and 2 years post treatment. The EORTC QLQ-C30 is an established instrument for measuring quality of life in cancer patients and contains 30 items that measure five functional scales, global quality of life and several cancer related symptoms. The QLQ-BR23 questionnaire is a specific tool, which contains 23 items measuring functioning and symptoms related to breast cancer [19]. Life quality assessment should include: pain/dysaestesia (yes/no), frequence/duration (no/intermittent/permanent) and treatment necessity (no/intermittent/permanent).

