**Discussion:**

Primary objectives of the study are the evaluation of the cosmetic results 6 weeks and 2 years post treatment and the 2- and 5-year local recurrence rates for the two different radiotherapy strategies. Secondary objectives are long term overall survival, disease free survival and quality of life.

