### Study objectives

Primary objectives of the study are cosmetic result and local control rate after radiotherapy. The cosmetic result will be evaluated at 6 weeks and 2 years post radiotherapy. Local control will be evaluated at 2 and 5 years post treatment.

Secondary objectives of the trial are quality of life at 6 weeks and 2 years after radiotherapy, as well as overall survival and disease free survival at 6 weeks, 2, 5, 10 and 15 years post radiation treatment.

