### Statistical analysis

#### Primary criteria and hypotheses

Primary aim of the study is the assessment of the cosmetic outcome and local control at 2 years after breast radiotherapy. The question to be investigated is whether intensity modulated radiotherapy (IMRT) is, in spite of the reduced treatment duration, at least equivalent to conventional therapy. The combined null hypothesis (H_0_) is "Conventional therapy is better by more than a pre-specified margin than IMRT with respect to the cosmetic outcome or local control". The alternative hypothesis (H_1_) is: "IMRT is better, or worse at most by the pre-specified margin than conventional radiotherapy with respect to both cosmetic outcome and local control". The null hypothesis will be rejected, if the lower limits of both 95 per cent confidence intervals for the effect of IMRT vs. standard are higher than the respective non-inferiority margin. The non-inferiority margins are set to a relative risk of 4.67 for local control and 1.54 for the BRA measurement of cosmesis. The non-inferiority margin for local control seems very high but it is expected to correspond to an absolute risk difference of 7 percent (from 98 to 91 per cent). The adoption of local control as a primary endpoint despite low probability of loss of local control honours the importance of the endpoint and safeguards against too severe concessions in this respect. As the total radiation dose is equivalent for both arms though, it is expected that there will be no difference in local control.

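### Local control is co-primary, but the only relapse class containing the breast also pools nodes and field borders, so rates, margin and power are not tied to one event

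*Protocol article*

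**What the plan says.** **Endpoint.** Under Study objectives: "Primary objectives of the study are cosmetic result and local control rate after radiotherapy". The abstract's Discussion paragraph names "the 2- and 5-year local recurrence rates for the two different radiotherapy strategies". Under Primary criteria and hypotheses: "Primary aim of the study is the assessment of the cosmetic outcome and local control at 2 years after breast radiotherapy". Analysis methods puts local control in an age-adjusted Cox model and does not say what the event is.

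**Margin and power.** "The non-inferiority margins are set to a relative risk of 4.67 for local control and 1.54 for the BRA measurement of cosmesis". The same section equates the first margin with a fall in local control from 98% to 91%. Sample size calculation gives 251 patients per arm, 10% drop-out and 82.5% power for local control.

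**Relapse classes.** These appear only under Evaluation, and there are two. The first: "Tumor manifestations within the residual breast, the regional lymphatics (axillary, parasternal, infra-/supraclavicular) or the radiation field borders are defined as locoregional relapse". The second: "Other types of tumor recurrence are considered distant metastases". There is no class for the breast alone.

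**Second cancers.** Also under Evaluation, they need histological confirmation, and "The results of the analysis should not be consistent to the original histology of the primary tumor". Contralateral breast cancer is not mentioned.

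**The concern.** Someone coding events for the Cox model has two choices. They can treat locoregional relapse as the event, which brings in axillary, parasternal and supra-/infraclavicular nodes and field borders. Or they can set up an in-breast category that the article does not contain. The article does define relapse, but with a scope that differs from its own primary endpoint.

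The choice matters because this is a non-inferiority comparison with few events. Events that occur equally in both arms pull the hazard ratio towards 1 and narrow the confidence interval, and both favour a non-inferiority conclusion. If the margin was set for in-breast control and the count includes nodes, the test is easier to pass than its nominal level implies.

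The second-cancer rule is a separate matter. A new contralateral breast primary often cannot be told from the first tumour by histological type alone. Under the rule, one that matches is not a second cancer. The article has an interest in counting such cases: both arms limit the contralateral breast dose, and Follow up justifies 15 years of documentation partly by secondary cancer.

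**Working it through.** **Inputs from the article:** local control 98% (conventional) and 91% (margin); margin 4.67; 251 per arm less 10%, about 226; no true difference expected; 95% confidence interval, so one-sided 2.5% if two-sided. **Assumed, not in the article:** a share f of control-arm events is nodal, with the same nodal hazard in both arms, added to a 2% in-breast rate; constant hazards; analysis at 2 years.

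**1. The margin.** ln(0.91)/ln(0.98) = 4.668, so 4.67 reproduces as a hazard ratio. The simple risk ratio would be 9%/2% = 4.50.

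**2. The stated power.** Counting in-breast events only, 2 × 226 × 0.02 = 9.0 events. Schoenfeld: Φ(√9.04/2 × ln 4.67 − 1.96) = Φ(0.357) = 64%. With 251 per arm it is 68%. The stated 82.5% is not reproduced at 2 years; it needs about 15 events.

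**3. Power depends on the definition.** Adding 1% nodal relapse in each arm gives 2 × 226 × (1 − 0.98 × 0.99) = 13.5 events and 81% power when the arms are equal.

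**4. Dilution at the margin.** With a true in-breast hazard ratio of 4.67, composite HR = 4.67(1 − f) + f. Non-inferiority is declared when the upper 95% limit is below 4.67. Normal approximation: Φ(ln(4.67/HR)/SE − 1.96), with SE = √(1/d₁ + 1/d₀), where d₁ and d₀ are the expected events in the IMRT and conventional arms.

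| f | Composite HR | d₁ / d₀ | False non-inferiority, approximation | Cox simulation (6,000 trials) |
|---|---|---|---|---|
| 0 | 4.67 | 20.3 / 4.5 | 2.5% | 2.8% |
| 0.20 | 3.94 | 21.4 / 5.6 | 5.5% | 6.3% |
| 0.33 | 3.46 | 22.4 / 6.7 | 10.1% | 11.4% |
| 0.40 | 3.20 | 23.1 / 7.5 | 14.4% | 16.1% |

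Example for f = 0.20: SE = √(1/21.4 + 1/5.6) ≈ 0.47; ln(4.67/3.94) ≈ 0.17; Φ(0.36 − 1.96) ≈ 5.5%. This f corresponds to about 0.5% nodal relapse at 2 years, roughly one extra control-arm event (5.6 against 4.5).

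**5. If the 2% already includes nodal events.** With nodal share s, a composite HR of 4.67 tolerates an in-breast HR of (4.67 − s)/(1 − s): 5.08 at s = 10%, 5.89 at 25%, 8.34 at 50%.

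**6. If nodal relapse differs by arm.** Take an in-breast HR of 1, 2% in-breast and 1% nodal relapse in the control arm. A nodal HR of 2 gives (2 + 2)/3 = 1.33, and a nodal HR of 4.67 gives (2 + 4.67)/3 = 2.22. Both move away from non-inferiority.

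**7. Contralateral cancers.** No arithmetic applies. A same-histology contralateral primary fails the second-cancer rule. If it is called a recurrence, it goes to distant metastases; if not, it has no class. Neither route leads into local control.

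**The case against.** **The article never makes locoregional relapse the primary event.** This is correct. A reader might infer from Evaluation that nodal relapses are counted by rule and that the trial is therefore biased. The documents do not support that: the residual breast is listed as a distinct site, and the plain reading of local control as in-breast control stays open. What stands is an unresolved mismatch between the endpoint and the only classification offered. It is more than detail left to a fuller document, because the article gives a definition and its scope does not match the endpoint.

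**Nodal relapse may depend on arm.** Irradiation of the lymphatics equalises the indications for nodal treatment, not its delivery. Under Treatment planning and radiation therapy the arms differ in technique, clinical target volume, margins and image guidance, and in certain cases the target includes the lymphatics. So a push towards non-inferiority is conditional, and step 6 shows that it can reverse.

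**The error rates apply to one reading.** They need the margin to refer to one event and the count to another. If 98%, 91% and 4.67 all describe a locoregional endpoint, its error rate is nominal, though the tolerated in-breast ratio is then larger (step 5). If all describe in-breast control, there is no dilution. The article does not say which.

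**The power gap has other possible causes.** A reader might take 64% against 82.5% as proof that nodal events were included in the planning. It is not: simulating follow-up of all patients to 5 years gives 91–94%, so longer follow-up could supply the events.

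**Contralateral cancers.** A reader might infer that they are always counted as distant metastases. The text sends only recurrences there, and a new primary is not one; at the least, it is left unclassified.

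**Conclusion.** The concern holds as a definition mismatch in a confirmatory endpoint. The sites that end local control are not fixed, so 98%/91%, 4.67 and 82.5% cannot be assigned to one event.

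Its possible size is material. False non-inferiority on the local-control component would be about 6%, 11% or 16% instead of 2.5%, for nodal shares of 20%, 33% or 40%. That rests on four conditions: a margin meant for in-breast control, nodal events counted on top of a 2% in-breast rate, equal nodal hazard by arm, and shares that are assumed. The figures concern this component alone; the trial must also pass on cosmesis. Without the equal-hazard condition the direction is open.

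The second-cancer rule gives a wrong classification if followed. It distorts second-cancer counts and possibly the type of disease-free-survival event, and has no bearing on the co-primary ratio.

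**What to change.** 1. Define loss of local control as recurrence in the ipsilateral residual breast, and state that regional nodal relapse, and field-border relapse outside the breast, do not count.
2. Tie 98%, 91% and 4.67 to that definition, and restate the power for it: about 9 events by 2 years and about 64% by Schoenfeld with 226 per arm. If the 82.5% relied on longer follow-up, say so.
3. Report regional relapse and the locoregional composite as secondary endpoints.
4. Count a new tumour in the contralateral breast as a second primary whatever its histology, unless there is evidence that it is a metastasis.

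The cost is a few sentences, a revised power statement and, if the eCRF (not shown) lacks one, a site-of-relapse item. No new procedures are needed. The downside is real: fewer primary events than a locoregional count, and a less favourable stated power.

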### Statistical analysis

#### Primary criteria and hypotheses

Primary aim of the study is the assessment of the cosmetic outcome and local control at 2 years after breast radiotherapy. The question to be investigated is whether intensity modulated radiotherapy (IMRT) is, in spite of the reduced treatment duration, at least equivalent to conventional therapy. The combined null hypothesis (H_0_) is "Conventional therapy is better by more than a pre-specified margin than IMRT with respect to the cosmetic outcome or local control". The alternative hypothesis (H_1_) is: "IMRT is better, or worse at most by the pre-specified margin than conventional radiotherapy with respect to both cosmetic outcome and local control". The null hypothesis will be rejected, if the lower limits of both 95 per cent confidence intervals for the effect of IMRT vs. standard are higher than the respective non-inferiority margin. The non-inferiority margins are set to a relative risk of 4.67 for local control and 1.54 for the BRA measurement of cosmesis. The non-inferiority margin for local control seems very high but it is expected to correspond to an absolute risk difference of 7 percent (from 98 to 91 per cent). The adoption of local control as a primary endpoint despite low probability of loss of local control honours the importance of the endpoint and safeguards against too severe concessions in this respect. As the total radiation dose is equivalent for both arms though, it is expected that there will be no difference in local control.

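### The primary decision rule pairs a benefit-scale test (lower limit above the margin) with a harm-scale margin for local control, so as written it contradicts the stated alternative hypothesis

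*Protocol article*

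**What the plan says.** All the wording at issue is in the Protocol article, Primary criteria and hypotheses.

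- Null hypothesis: "Conventional therapy is better by more than a pre-specified margin than IMRT with respect to the cosmetic outcome or local control".
- Alternative: "IMRT is better, or worse at most by the pre-specified margin than conventional radiotherapy with respect to both cosmetic outcome and local control".
- Condition for rejecting the null: "lower limits of both 95 per cent confidence intervals for the effect of IMRT vs. standard are higher than the respective non-inferiority margin".
- Margins: "The non-inferiority margins are set to a relative risk of 4.67 for local control and 1.54 for the BRA measurement of cosmesis".
- Meaning of the first margin: "it is expected to correspond to an absolute risk difference of 7 percent (from 98 to 91 per cent".
- Design expectation: "it is expected that there will be no difference in local control".

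Analysis methods estimates local control as the treatment parameter of a Cox model, and cosmesis by a linear model adjusted for age and baseline. Sample size calculation states 251 patients per arm, 10% drop-out, and power of 97.5% for cosmesis and 82.5% for local control.

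**The concern.** A rule of the form 'lower limit above the margin' suits an effect measure on which larger is better for the experimental arm. The margin is then below the null value: under 1 for a ratio, negative for a difference. The local-control margin is far above 1, and the text links it to poorer control with IMRT. On that scale non-inferiority is shown when the upper limit lies below the margin. The rule and the margin come from opposite scales.

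This is the only success criterion given for the combined primary hypothesis. Applied literally, it cannot confirm the equivalence that the trial expects, and it is satisfied only by data showing what the trial wants to rule out. An analyst who noticed this after unblinding would have to reverse the primary test without written authority.

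**Working it through.** **Inputs.** From Primary criteria and hypotheses: contrast IMRT versus standard, 95% intervals, margin 4.67, 2-year control of 98% against 91%, no expected difference. From Sample size calculation: 251 per arm less 10%, so 251 × 0.9 = 225.9, about 226 evaluable. From Analysis methods: Cox model.

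**Step 1: reproduce the margin.** Under proportional hazards the hazard ratio is ln(S_IMRT)/ln(S_standard) = ln(0.91)/ln(0.98) = 4.668, which matches 4.67. The plain ratio of failure risks is 0.09/0.02 = 4.50 and does not match. A ratio of control probabilities is impossible: 0.91/0.98 = 0.93, and with 98% in the standard arm that ratio cannot exceed 1/0.98 = 1.02. So 4.67 is a hazard ratio for local failure, as the Cox model would give, and larger is worse for IMRT.

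**Step 2: compare the rule with the hypotheses.** On this scale the alternative is HR ≤ 4.67 and the null is HR > 4.67. A lower limit above 4.67 is evidence for HR > 4.67. The rule rejects the null when the data support it.

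**Step 3: try the benefit-scale reading.** If the effect were inverted so that larger favours IMRT, the margin would have to be 1/4.67 = 0.214. Keeping 4.67 on the inverted scale would demand more than a 4.67-fold reduction in failure, which is superiority. Neither orientation makes the printed rule a test of the stated alternative.

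**Step 4: approximate chance of passing with no true difference.** Expected events by 2 years: 2 × 226 × 0.02 = 9.04. Standard error of the log hazard ratio: about 2/√9.04 = 0.665. Log margin: ln 4.67 = 1.541. The lower limit exceeds the margin only if the estimated log hazard ratio exceeds 1.541 + 1.96 × 0.665 = 2.845, an estimated HR above about 17. Under HR = 1 that is 2.845/0.665 = 4.28 standard errors from zero, a probability of about 1 in 100,000.

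(The log margin equals the printed BRA margin to two decimals. The article does not say whether this is coincidence and nothing here relies on it, but it is one more reason to state what 1.54 is.)

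**Step 5: simulation, local control only.** Exponential times, 98% 2-year control in the standard arm, 226 per arm, censoring at 2 years, Cox model with Wald 95% interval. There were 9,999 runs at HR 1 and 4,000 at the others. Runs without events in one arm have no finite interval and count as not passing.

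| True HR | 2-year control with IMRT | Lower limit > 4.67 (as written) |
|---|---|---|
| 1 | 98% | 0.00% |
| 4.67 | 91% | 0.05% |
| 10 | 82% | 26.5% |
| 15 | 74% | 76.3% |
| 20 | 67% | 96.1% |

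With the limit and direction reversed (upper limit below 4.67), the pass rate at a true HR of 4.67 is 3.25%, close to the nominal one-sided 2.5%. The reversed rule therefore behaves as a non-inferiority test at the margin.

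**The case against.** **Intent.** Both hypotheses are stated in the right direction, and the literal rule could not give the quoted powers under no difference. A reader might infer that the trial was designed or sized around an inverted test. The documents do not support that: the likeliest explanation is a standard benefit-scale sentence placed beside harm-scale margins. The full analysis plan, not shown, may have it right. This stands as a defence of the aim, not of the published sentence, which nothing else in the article corrects.

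**BRA.** A reader might infer that both margins are ratios on scales where larger is worse. The article does not establish this for BRA. The term relative risk is clearly attached only to 4.67, and a linear model naturally yields a difference. The Evaluation section names the score and its reference points but does not say that higher is worse, although the name (breast retraction assessment) suggests it. This objection stands, so the proof here rests on local control alone. That suffices because both limits must pass.

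**Consequence.** A reader might infer that proven inferiority on local control would by itself be declared non-inferiority. It would not: the rule needs both lower limits above their margins, so a false claim also needs the BRA limit to exceed 1.54. The table covers one of two required conditions and is an upper bound for the combined rule.

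**Power.** In the simulation the reversed rule passes in about 60% of trials at HR 1, and a reader might infer that the stated 82.5% is wrong. That figure assumes censoring at exactly 2 years. With 3 years it is about 77% (226 per arm) to 81% (251 per arm). The article gives no follow-up or accrual inputs for its own simulation, so the comparison is inconclusive. The directional error does not depend on it.

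**Conclusion.** The decision rule is wrong as written. For local control it accepts only evidence that IMRT is worse than the margin, contrary to the alternative hypothesis in the same paragraph. Under the design's own expectation of no difference, the chance of success is essentially zero (0 of 9,999 simulated trials; about 1 in 100,000 by the normal approximation), against a stated 82.5%.

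The direction follows from the article's own rates and needs no simulation. The sizes assume 226 evaluable per arm, exponential failure times, 2-year censoring and Wald intervals. The conclusion is confined to a mismatch of scale and direction in the written rule; it does not extend to the trial's aim, its sample size or the orientation of the BRA margin. It must still be corrected, because the sentence decides the primary result.

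**What to change.** Replace the rejection sentence with one to this effect: the null hypothesis is rejected if the upper limit of the two-sided 95% confidence interval for the hazard ratio of local failure (IMRT versus standard) is below 4.67 and the upper limit of the two-sided 95% confidence interval for the BRA effect (IMRT versus standard) is below 1.54.

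Add two statements: whether 1.54 is a difference in BRA units or a ratio, and that a higher BRA means worse cosmesis, which the corrected sentence assumes.

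If a benefit scale is preferred, keep lower limits but re-express the margins:

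- Local control: lower limit above 1/4.67 = 0.214.
- BRA: lower limit above -1.54 if 1.54 is a difference, or above 1/1.54 = 0.65 if it is a ratio.

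Taking reciprocals of both margins without first settling the BRA scale could put a new error into the rule.

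The cost is one corrected sentence and a short definition, with no change to recruitment, assessments or data collection. The analysis plan should be checked for the same wording, and the correction dated before the primary analysis.
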